### Outcome measures

2.6

Assessments will be conducted at baseline and at 5 weeks (5W), 9 weeks (9W), and 13 weeks (13W). Table 3 shows the schedule for the assessments.

**Table 3 T3:**
[figure not shown]
Schedule for the treatment and the outcome measurements.

The primary outcome is the mean change in the Neck Pain and Disability Scale (NPDS) score at 9W. NPDS consists of 20 items that assess neck movement, neck pain on emotion, and cognition, neck pain intensity, and the level of interference with daily life activity.^[35]^ Each item consists of a 100-mm visual analogue scale (VAS) with numeric anchors of 0 (normal), 1, 2, 3, 4, and 5 (most severe) at 20 mm intervals. The total score is evaluated as 100 points, and the higher the score, the more severe the pain and dysfunction. The NPDS score is valid only if the subject self-checks more than 17 items.^[7]^ This trial uses the Korean version of the NPDS with the reliability and validity already verified.^[36]^

The secondary outcomes include NPDS scores at other time points (5W, 13W), the clinical relevance, cervical spinal angle, Beck Depression Inventory II (BDI-II), Beck Anxiety Inventory (BAI), EuroQol-Five Dimension 3 level version (EQ-5D-3L), Pressure Pain Threshold (PPT), and Patient Global Impression of Change (PGIC).

The clinical relevance will be assessed by using minimal clinically important difference (MCID). MCID is the minimum difference that a patient can feel to be clinically effective.^[37]^ It is recommended that MCID should be considered in the assessments of chronic pain.^[38]^ According to a study that verified the clinical relevance of the NPDS, the MCID was found to be greater than 11.5 points.^[22]^ In this trial, the clinical relevance for result of this trial will be assessed by comparing the percentage of subjects indicating an improvement of more than 11.5 points (MCID) on the NPDS, of more than 30% (moderate CID), and of more than 50% (substantial improvement), respectively, between the 2 groups.^[38]^

Cervical spinal angle is the angle between the straight lines that connect the posterior edges of the C2 and C7 vertebrae, and in the normal case, it is between 31° and 40°.^[39,40]^ In patients with CNP, the cervical spinal angle tends to decrease compared to acute,^[41,42]^ and there is a significant relationship between neck pain and angle in the case of less than 20°.^[43]^ In this trial, the cervical spinal angle of the baseline will be compared with that of 9W.

Depression and anxiety are all highly correlated with neck pain.^[44]^ This study uses the Beck Depression Inventory II (BDI-II) and Beck Anxiety Inventory (BAI) as depression and anxiety measures, respectively.^[45,46]^ The BDI-II consists of 21 items, each of which is rated on a Likert scale ranging 0 to 3, with a total score ranging 0 to 63 points. The BAI also consists of 21 items, each of which is rated ranging 0 to 3, with a total score ranging 0 to 63 points. For this trial, the Korean versions of BDI-II and BAI will be used.^[47,48]^

EuroQol-Five Dimension 3 level version (EQ-5D-3L) is the most widely used questionnaire to assess the quality of life, and consists of the EQ-5D index and the EQ-5D VAS. The Korean version of the EQ-5D-3Lwill be used for this trial.^[49,50]^

Pressure Pain Threshold (PPT) will be measured twice on both sides of the neck by digital algometer (FPX 25, Wagner Instrument., Greenwich, CT), and the mean value (kg/cm^2^) will be used. The 3 measurement points are as follows;

1.GB21: the upper trapezius,2.the insertion point of the levator scapulae muscle, and3.the point extending 1.5 cm outward from the sixth cervical vertebra.^[51]^

Patient Global Impression of Change (PGIC) will be used.^[52]^ Subjects will assess for the improvement of symptoms they have felt before and after treatment. The subjects will choose one item from 7 categories of responses to by how much the neck pain has been reduced compared with before treatments in this trial.

### Adverse events

2.7

In this trial, AEs are defined as all unintentional medical findings newly observed during this clinical trial. The researcher examines the AEs at each visit based on vital sign, history taking, and other examinations. Also, the subject will be instructed to voluntarily report AEs frequently, and the researcher should confirm them through medical examination. All identified AEs will be recorded on the CRF, without reference to their association with interventions. If severe AEs (SAEs) occur, the researchers will temporarily discontinue the treatment of the subject in this clinical trial. If continuous treatment is judged to be hazardous to the subject and the AE is associated with treatment, the researchers will permanently discontinue the participation of the subject in this trial.

Local discomforts after the TEA treatments could generally last about 2 days. Local discomforts that last more than 2 days after TEA treatment will be classified into AE from 2 to 7 days (delayed AE) and AE for more 7 days, and will be analyzed and reported. This is based on the previous study,^[53]^ which reported AEs from 1 to 7 days after dry needling treatment as delayed AEs, and reflects that local discomforts after TEA treatment may last longer than simple dry needling, due to the continuous stimulation by PDO.

### Statistical analysis

2.8

All statistical analyses will be conducted as a 2-sided test, and the significance level will be set at 5%. The statistical program SAS Version 9.4 (SAS Institute Inc., Cary, NC) will be used. Multiple imputations will be used when missing values are encountered.

The data obtained from this trial will be analyzed by Full Analysis Set (FAS) and Per Protocol (PP) set. The FAS refers to the analysis method of minimizing the subjects excluded from the analysis among the randomly assigned subjects by excluding the subjects from the analysis only when there is a justifiable reason. The PP refers to the method of analyzing a group of subjects who have participated in more than 75% (3 or more TEA, 6 or more PT) of the interventions according to this clinical trial's protocol, for whom all of the assessment variables have been completely measured, and who have not violated this trial's protocol.

The descriptive statistics on the variables, such as demographic characteristics, sex, age, medical history, and drug administration will be presented for each treatment group. To verify the heterogeneity between the 2 groups at baseline, for continuous data, the mean and SD will be presented and analyzed using a Wilcoxon rank sum test or independent *t* test. The 95% confidence intervals will be provided as needed. For categorical data, frequency and percentiles will be presented and analyzed using the Fisher Exact test or Chi-square test. The primary outcome variable is the mean changes of NPDS score at 9W compared with the baseline. Analysis of covariance (ANCOVA) will be used with NPDS score at baseline as covariate and each treatment group as fixed factor. Secondary outcome variables will be analyzed in the same way as the primary outcome variables. If outcome variables are categorical variables, they will be analyzed using the Fisher Exact test or Chi-square test. The Wilcoxon signed-rank test or Paired *t* test will be used to analyze differences in measured values between pre- and post-treatment in each group. Repeated measures analysis of variance (RM-ANOVA) will be performed to examine the differences in symptom change by visit. Dunnett procedure will be used for multiple comparisons. As needed, a subgroup analysis of outcome variables such as demographic variables (age, gender, duration of illness at baseline, etc.), whether or not rescue medications were taken, and the amount of rescue medications taken can be performed.

The safety assessment will be performed by analyzing the incidence of AEs and SAEs. The collected safety data will be summarized and described descriptively. AEs will be recorded and presented as descriptive statistics.

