#### Thread embedding acupuncture

2.5.1

Table 2 summarizes the detailed information of TEA treatment.^[10,15,23–34]^ The patients in the TEA group will receive a total of 4 TEA treatments over 4 weeks. The TEA with a diameter of 29 gauge, and a length of 30 or 40 mm (29X36DF, 29046DF, Dongbang Medical Co., Seongnam, Republic of Korea) will be selectively used considering the depth of penetration and the muscle condition of the subject (Fig. 2). Patients are to be placed in a sitting position, with the appropriate treatment site exposed. The practitioner will insert the disposable sterile TEA, and immediately withdraws it, without further stimulation. Among the pre-selected acupuncture point pools, 4 to 8 acupuncture points will be selected per side considering the region of pain, meridian diagnosis, motion, palpation with controlled finger pressure, and spinal malalignment. The practitioner will perform a perpendicular or oblique insertion on the paravertebral point of dorsal aspect, and oblique or transverse insertion on the lateral side of the thorax and cervical vertebrae to avoid the risk of damaging critical structures, such as the external jugular vein, or common carotid artery. Before and after the treatment, Practitioners will sterilize the neck region with cotton saturated with 78% alcohol. On the day of TEA treatment, strong motion or stimulation of the treated sites will be prohibited to prevent the embedded thread from protruding. All TEA treatments will be conducted by Korean Medicine doctors (KMDs) who have had TEA treatment experience of over 3 years.

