#### Physical therapy

2.5.2

The patients in the PT group will receive a total of 8 PT treatments over 4 weeks. In patients with chronic pain, PT has been performed 2 to 3 times a week with acupuncture, whereas TEA procedures are usually applied once a week, or once every 2 weeks.^[27–33]^ Based on the results of previous clinical studies that evaluate the effect of adding TEA to usual care in the treatment of patients with non-specific CNP by using NPDS,^[15]^ we have assumed that once-a-week treatment with TEA would have an equivalent clinical effect to 2 or 3 PTs per week. Interferential current therapy (ICT) (EDiT 400, Nemectron, Karlsruhe, Germany) and heat therapy using hot pack (DS-3860H, Daeshinelc Co, Bucheon, Republic of Korea) will be applied to the PT group in this trial. With the subject in the prone position, the ICT pads will be attached to 4 points of the neck pain region, and the neuromuscular system is stimulated by crossing 2 currents (4000 or 4100 Hz) to cause interference. Depending on the subject's condition, it will be applied with an intensity of 5 to 20 mA. An electric-heated hot pack heated to 40 to 50°C will be applied to the neck.^[34]^ ICT and hot pack will be applied at the same time, and after attaching the ICT pad first, hot pack will be applied on it for about 15 minutes per session. All PT treatments will be conducted by KMDs who have had clinical experience of over 2 years. After the trial is completed, for compensation, the subjects in the PT group will receive one session of TEA treatment, upon request.

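### The per-protocol rule contradicts its own session counts at exactly 75%, and its all-variables condition drops treated subjects from the primary PP analysis for unrelated missing data

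*Protocol article*

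**What the plan says.** Section 2.8 (Statistical analysis) of the protocol article names two analysis sets, the full analysis set (FAS) and the PP set. One sentence gives the PP set three conditions:

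- **Attendance.** Subjects must have "participated in more than 75% (3 or more TEA, 6 or more PT) of the interventions".
- **Data.** They must be subjects "for whom all of the assessment variables have been completely measured".
- **Conduct.** They must not have violated the protocol.

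The session totals are fixed elsewhere. Section 2.5.1 states: "The patients in the TEA group will receive a total of 4 TEA treatments over 4 weeks". Section 2.5.2 states: "The patients in the PT group will receive a total of 8 PT treatments over 4 weeks".

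Section 2.6 (Outcome measures) says: "The primary outcome is the mean change in the Neck Pain and Disability Scale (NPDS) score at 9W". Assessments take place at baseline and at 5, 9 and 13 weeks. Besides NPDS at 5 and 13 weeks, the secondary outcomes are the responder percentages, cervical spinal angle (baseline against 9 weeks), BDI-II, BAI, EQ-5D-3L, PPT and PGIC.

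On missing data, section 2.8 says: "Multiple imputations will be used when missing values are encountered".

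**The concern.** The attendance condition gives a percentage and a pair of counts, and they disagree for a subject who attends exactly 3 TEA or exactly 6 PT sessions. That subject is the borderline case the rule exists to settle. PP is one of only two stated analysis sets, and patients and practitioners know the allocation (section 2.4), so membership should not be open to decision after the data are seen.

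The data condition is not tied to the outcome being analysed. The primary outcome needs NPDS at baseline and at 9 weeks. As written, a subject who attended the sessions and has both values is still removed from the PP analysis of that outcome if, say, a BAI form or a PPT reading is missing. A missing secondary measure says nothing about adherence to treatment. The rule therefore discards usable primary-outcome data without making the set any more per-protocol.

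**Working it through.** **1. The plan's own figure.** Inputs: 4 TEA sessions (section 2.5.1), 8 PT sessions (section 2.5.2), and counts of 3 and 6 (section 2.8).

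- TEA: 3/4 = 0.750
- PT: 6/8 = 0.750

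Both counts are exactly 75%. They match a rule of at least 75%, not one of strictly above 75%.

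**2. The words taken literally.** The smallest whole number strictly above 0.75 × 4 = 3 is 4, and 4/4 = 100%. The smallest whole number strictly above 0.75 × 8 = 6 is 7, and 7/8 = 87.5%. The literal words would thus set a higher bar for TEA than for PT.

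**3. What turns on the reading.** The article gives no attendance rate. Assume each session is attended independently with probability p. The share excluded is 1 − P(X ≥ k), where X is binomial with 4 (TEA) or 8 (PT) trials.

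| p | Reading | TEA excluded | PT excluded |
|---|---|---|---|
| 0.95 | counts (≥3 of 4, ≥6 of 8) | 1 − 0.986 = 1.4% | 1 − 0.994 = 0.6% |
| 0.95 | literal (4 of 4, ≥7 of 8) | 1 − 0.815 = 18.5% | 1 − 0.943 = 5.7% |
| 0.90 | counts | 1 − 0.948 = 5.2% | 1 − 0.962 = 3.8% |
| 0.90 | literal | 1 − 0.656 = 34.4% | 1 − 0.813 = 18.7% |

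Under the counts the arms are nearly level. The large and uneven exclusions appear only if the counts are ignored.

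**4. The completeness condition.** The article gives no missingness rate, and the schedule (Table 3) is not shown, so only a range can be given. With a proportion q missing in each of m units, independently, the share of subjects lost is 1 − (1 − q)^m.

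- *Only whole visits missed*, at the three post-baseline visits (m = 3): q = 1% gives 1 − 0.99³ = 3.0%; q = 2% gives 1 − 0.98³ = 5.9%.
- *Every instrument at every visit missing independently*, with m = 19 assumed (NPDS, BDI-II, BAI, EQ-5D-3L, PPT and PGIC at three visits, 6 × 3 = 18, plus one spinal angle): q = 1% gives 1 − 0.99¹⁹ = 1 − 0.826 = 17.4%; q = 2% gives 1 − 0.98¹⁹ = 1 − 0.681 = 31.9%.

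Instruments completed at the same visit tend to go missing together, so the second pair is the pessimistic end of the range.

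**5. Sample size.** The stated figure reproduces: n = 2 × [20.67 × (1.960 + 0.842)/11.5]² = 50.7, so 51 per group; 51/0.80 = 63.75, so 64 per group and 128 in total. Neither problem enters this calculation.

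**The case against.** The case for leaving the sentence alone has real weight.

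- **The counts are explicit.** Anyone building the PP set would probably apply 3 and 6. The article uses the same loose phrasing in section 2.7, where discomfort lasting beyond 2 days is sorted into a class that starts at 2 days. This stands: the likely intent is clear, and the contradiction is one of wording.
- **A completer PP set is coherent.** It is strict, but it is not an error in itself, and a condensed article may leave per-outcome handling to a fuller document. This stands in part. The completeness condition is, however, stated here in unrestricted terms, so the point concerns a stated rule and not an omission. The sentence does not spell out visits, but even if it meant only the 9-week visit, a missing BAI or PPT would still remove a subject with a valid 9-week NPDS.
- **The FAS is also analysed.** It is defined to keep exclusions to a minimum, and multiple imputation is planned. This limits the consequence, although the article does not say which of the two sets leads.

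Four stronger readings are tempting, and the article does not support them:

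- *The PP set will be unbalanced by attendance.* That follows only from the literal words, against the explicit counts.
- *The completeness rule removes subjects unevenly or keeps those who are doing better.* Nothing in the article indicates missingness that differs by arm or by response.
- *A sixth to a third of subjects will be lost.* Those figures rest on an assumed 19 instrument-visits going missing independently.
- *Multiple imputation conflicts with a completer PP set.* Imputing in the FAS and restricting the PP set to complete subjects can stand side by side.

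**Conclusion.** The point holds in two limited parts.

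First, the attendance threshold is wrong as written. The percentage excludes a subject at exactly 3 of 4 TEA or 6 of 8 PT sessions, and the counts include that subject. This is arithmetic on the article's own numbers and needs no assumption. The counts are probably what was meant.

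Second, the completeness condition is wider than the primary PP analysis needs, and it can remove treated subjects who have both NPDS values. The size of that loss cannot be determined from the article. The range of about 3% to about 32% depends on an assumed 1% to 2% missing and on whether data go missing by whole visit or by single instrument. No difference between arms, and so no direction of bias, is shown.

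Severity is minor. The sample size is unaffected, and the FAS analysis does not depend on this sentence.

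**What to change.** Reword the PP definition in section 2.8, before data by group are examined:

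- Attendance: at least 75% of the planned sessions (3 or more of 4 TEA, 6 or more of 8 PT).
- Data, primary outcome: a valid NPDS at baseline and at 9 weeks, in place of completeness on all variables.
- Data, each secondary outcome: that outcome at baseline (where it is measured) and at its own visit.

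The cost is a short change to the analysis wording, with no change to recruitment, visits or data collection. The one downside is that the PP set will differ slightly between outcomes, so the number analysed should be reported with each.

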### Study design

2.2

This clinical trial will be performed as a 2-arm parallel design, randomized, controlled, assessor-blinded, stratified block (male, female), and clinical trial. Figure 1 shows the suggested flowchart of this trial. This study is to recruit 128 applicants, who meet the criteria of inclusion and exclusion (Table 1).^[14,15,21]^ A total of 128 patients with CNP are to be recruited from Daejeon University Dunsan Korean Medicine Hospital. Applicants will be recruited through advertisements posted on bulletin boards at hospitals, subway stations, apartments, subway cars, hospital homepages, newspapers, etc. Recruitment commenced in April 2019, and the trial is expected to end in December 2019.

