**Table 1 T1:**
[figure not shown]
Inclusion and exclusion criteria.

All applicants will receive a full explanation of this trial's protocol and will be provided an informed consent form and written explanation. Also, radiography and blood tests (including liver function test, blood clotting factors, inflammation-related enzymes, etc.) will be conducted at screening visit. Participants who are judged to be eligible for this trial according to criteria will be randomly assigned in a 1:1 ratio to either the TEA group, or the PT group. The interventions will begin within 2 weeks of the screening. The subject of the TEA group will receive a total of four TEA treatments over 4 weeks, while the subject of PT group will receive a total of eight PT treatments over 4 weeks, followed by 3 follow-up visits, at 5, 9, and 13 weeks.

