### Randomization and blinding

2.4

Randomization will be conducted so as not to be biased, and be blinded to subjects and researchers. Statisticians who are not involved in the conduct and evaluation of clinical trials will randomly assign 64 patients to each group with the same probability of being selected, using the statistical program SAS Version 9.4 (SAS Institute, Inc., Cary, NC). Stratified block randomization will be used. The generated randomization table will be kept by independent statisticians and the file will be protected from disclosure.

In this trial, blinding of practitioner and subject is impossible in intervention, due to the characteristics of the procedure. However, it is designed to as much as possible be assessor-blinded to control bias. Assessments will be conducted by researchers who have not performed the intervention and randomization. The assessor will ask only simple questions about the evaluation items and the contents to fill out the case report form (CRF). The assessor does not know what kind of treatment the subject is receiving.

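### Randomisation is stratified by sex, but the stated primary ANCOVA, and the continuous secondary analyses that follow it, leave sex out

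*Protocol article*

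**What the plan says.** Section 2.2 (Study design) describes the trial as "randomized, controlled, assessor-blinded, stratified block (male, female), and clinical trial", and patients are to be "randomly assigned in a 1:1 ratio to either the TEA group, or the PT group". Section 2.4 (Randomization and blinding) confirms: "Stratified block randomization will be used". Sex is the only stratification factor named.

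Section 2.8 (Statistical analysis) gives the primary model for change in NPDS at 9 weeks: "Analysis of covariance (ANCOVA) will be used with NPDS score at baseline as covariate and each treatment group as fixed factor". It continues: "Secondary outcome variables will be analyzed in the same way as the primary outcome variables". Categorical outcomes go elsewhere: "If outcome variables are categorical variables, they will be analyzed using the Fisher Exact test or Chi-square test".

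In the efficacy analyses sex appears only as a variable for an optional subgroup analysis: "As needed, a subgroup analysis of outcome variables such as demographic variables (age, gender, duration of illness at baseline, etc". Nothing in the article adds sex to a model or explains its omission.

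**The concern.** Blocks within sex keep the two arms close to balanced for sex. Whatever sex contributes to NPDS change therefore largely cancels from the difference between arms, and the true sampling variance of that difference is smaller than under simple randomisation. A model without sex does not recognise this. It leaves the between-sex variation in the residual and computes the standard error as if the stratification had not happened.

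If sex is prognostic after baseline NPDS is accounted for, three things follow: confidence intervals are too wide, the test runs below the 5% level set in section 2.8, and power is lower than the same data could give. The continuous secondary outcomes inherit the model and the problem.

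This is not a detail left to a fuller document. The sentence names both the covariate and the fixed factor and reads as a complete model, and that model does not match the design.

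**Working it through.** **Inputs from section 2.3:** difference 11.5, SD 20.67, two-sided 5%, power 80%, 51 evaluable per group, 20% dropout, 64 per group. The two-sided 5% level is also in section 2.8.

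**Assumption:** R² is the share of residual variance (after baseline NPDS) explained by sex. The documents give no value, so a range is shown. SD 20.67 is taken as the residual SD when sex is ignored.

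**Step 1: the plan's own figure.** n = 2(1.960 + 0.842)² × 20.67² / 11.5² = 50.7, so 51 per group. 51 / 0.8 = 63.75, so 64 per group and 128 in total. The stated figures reproduce. Power at 51 per group is 80.2% by the normal approximation and 79.5% by the noncentral t. None of this depends on a sex term.

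**Step 2: formulas, with sex balanced across arms.** Let d = 11.5 / 20.67 = 0.556, so d√(51/2) = 2.809.
- Reported SE / true SE without sex in the model: 1/√(1−R²)
- Type I error without sex: 2[1 − Φ(1.96/√(1−R²))]
- Power without sex: Φ((2.809 − 1.96)/√(1−R²))
- Power with sex: Φ(2.809/√(1−R²) − 1.96)

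Worked case, R² = 0.10: 1/√0.9 = 1.054. Type I error is 2[1 − Φ(2.066)] = 3.9%. Power without sex is Φ(0.895) = 81.5%; with sex it is Φ(1.001) = 84.2%.

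| R² | SE overstated | Type I error, no sex | Power, no sex | Power, with sex | Gain (points) |
|---|---|---|---|---|---|
| 0 | 0% | 5.0% | 80.2% | 80.2% | 0 |
| 0.02 | 1.0% | 4.8% | 80.5% | 81.0% | 0.5 |
| 0.05 | 2.6% | 4.4% | 80.8% | 82.2% | 1.4 |
| 0.10 | 5.4% | 3.9% | 81.5% | 84.2% | 2.7 |

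**Step 3: simulation with 102 analysed patients.** There were 20,000 runs per scenario, with blocks of 4 within sex and 70% women (both assumed), and baseline in both models.

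| R² | Type I error, without / with sex | Power, without / with sex |
|---|---|---|
| 0 | 5.0% / 5.0% | 78.6% / 78.5% |
| 0.05 | 4.6% / 5.1% | 79.8% / 81.3% |
| 0.10 | 3.7% / 4.8% | 80.4% / 83.5% |
| 0.20 | 2.7% / 4.8% | 81.7% / 87.1% |

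At R² = 0.10 the mean reported SE without sex is 4.11, while the estimate's actual SD is 3.90. With sex in the model the two agree at 3.90. Simulation error is about 0.15 points for a 5% rate (√(0.05 × 0.95/20,000)) and 0.3 points for power (√(0.8 × 0.2/20,000)).

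**Step 4: dropout.** With 128 randomised and 20% random dropout, sex balance among those analysed is looser. At R² = 0.10 type I error is 4.0% without sex and 4.9% with it, and power is 80.2% and 83.3%. At R² = 0 adjustment loses nothing.

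**The case against.** The strongest reply concerns weight.

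- **The power target is met.** Section 2.3 takes no credit for covariates, and the formulas in the working put the unadjusted analysis at 80.5% to 81.5% for R² of 0.02 to 0.10. What is lost is an unbudgeted gain, not planned power. This stands.
- **The error is conservative.** There is no bias and no excess of false positives. This stands, and it limits the severity.
- **The harm is conditional.** It arises only if sex predicts change after baseline NPDS, and nothing in the article shows that it does. This stands, which is why a range is given.
- **Exact balance is assumed.** Allowing for 20% random dropout in a separate simulation without baseline NPDS gave unadjusted type I error of 5.1%, 4.7% and 4.1% at R² of 0.02, 0.05 and 0.10. At 0.02 this cannot be told from simulation noise. The power gain was unaffected (about 0.5, 1.5 and 3.3 points). Multiple imputation is not represented in any of these figures.
- **Scope.** Only continuous secondary outcomes inherit the ANCOVA. Categorical outcomes have their own tests, and the terms of the repeated-measures ANOVA are not listed. This stands.
- **The full document may already include sex.** Possibly, but the published sentence states a full set of terms, and a plan that added sex would differ from it.

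None of these points gives a reason to leave the stratification factor out.

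**Conclusion.** The concern holds. The article stratifies by sex and then states a primary model without it. Whenever sex is prognostic beyond baseline NPDS, the reported standard error is too large. For an assumed R² of 0.02 to 0.10 this means an SE overstated by 1.0% to 5.4%, a type I error of about 4.8% down to 3.9% (somewhat closer to 5% after dropout), and 0.5 to 2.7 points of power forgone at 51 per arm. If sex is unrelated to NPDS change, nothing is lost.

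The sizes rest on the assumed R² and near balance by sex; the simulations also assume the block size and the proportion of women. The point is one of efficiency and of agreement between design and analysis. Unbiasedness, protection against false positives and the 51/64/128 sample size are not in question. The correction should be made because it is almost free and settles the adjusted model before data are seen.

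**What to change.** Replace the model sentence in section 2.8 with: *ANCOVA of change in NPDS at 9W with treatment group and sex (stratification factor) as fixed factors and baseline NPDS as covariate.* State that continuous secondary outcomes use the same model, each with its own baseline value where one exists.

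Two consequences can be handled in the analysis plan. Sex, as a term of the analysis model, belongs in the imputation model. For the responder proportions, a sex-stratified test such as Cochran-Mantel-Haenszel, or logistic regression with sex, would be the matching choice.

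The cost is one sentence and one degree of freedom. Sex is already recorded, and neither the sample size nor trial conduct changes.

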### Sample size calculation

2.3

Based on the results of a previous study and clinical significance,^[15,22]^ we assume that the mean difference (δ) between the changes in NPDS before and after intervention in each group is 11.5, and the standard deviation (SD, σ) is 20.67. We have applied a significance level of 5%, a power of 80%. As a result, a minimum of 51 participants are needed for each group. Also, considering the expected dropout rate of 20%, at least 64 subjects per group, for a total of 128 subjects, are required. 

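### The 7-category PGIC falls under a Fisher or chi-square rule that ignores its ordering, at a cost of about one quarter to one half of the power of an ordinal test.

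*Protocol article*

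**What the plan says.** Section 2.6 (Outcome measures) lists PGIC among the secondary outcomes. It describes the response format as "The subjects will choose one item from 7 categories of responses", and the categories express how far the neck pain has fallen since before treatment. The scale is therefore ordered by its content. The same section defines three responder outcomes on the Neck Pain and Disability Scale (NPDS). The first is assessed by "comparing the percentage of subjects indicating an improvement of more than 11.5 points (MCID) on the NPDS", and the other two use thresholds of 30% and 50%.

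Section 2.8 (Statistical analysis) first sends secondary outcomes to the primary method, an ANCOVA with baseline NPDS and treatment group. It then makes a separate rule for one type of outcome: "If outcome variables are categorical variables, they will be analyzed using the Fisher Exact test or Chi-square test". Wilcoxon tests appear in two other places in that section. The rank-sum test is for baseline comparison of continuous data, and the signed-rank test is for within-group change. Neither is assigned to a between-group comparison of outcomes.

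**The concern.** The p-value of a 2x7 chi-square or Fisher test stays the same if the seven categories are shuffled. The test looks for any difference in pattern and spreads it over 6 degrees of freedom. The Introduction of the protocol article states a directional expectation, that thread embedding acupuncture will do better than physical therapy, and on a graded scale that would appear as a shift towards the improved end. A test that uses the order concentrates on such a shift with 1 degree of freedom.

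At stake is the chance that PGIC detects a real shift, and whether it yields an estimate with a confidence interval or only a p-value.

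**Working it through.** **The plan's own figure.** Section 2.3 says that the NPDS mean difference "in each group is 11.5, and the standard deviation (SD, σ) is 20.67", with 5% significance and 80% power. Section 2.8 makes all tests two-sided. Then

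n per arm = 2 × (1.960 + 0.842)² × (20.67 / 11.5)² = 2 × 7.849 × 3.231 = 50.7, so 51.

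This agrees with "a minimum of 51 participants are needed for each group". Dividing by (1 − 0.20) gives 51 / 0.8 = 63.75, so 64. Both stated figures reproduce. The standardised effect is 11.5 / 20.67 = 0.556. No power is stated for PGIC.

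**Assumed inputs.** The documents give no PGIC distribution or effect. The calculations use four control-arm distributions (spread out, skewed towards improvement, concentrated, uniform). The effect is a one-directional shift, given either as a common odds ratio or as a shift on an underlying normal scale. All seven categories are taken to be available and not collapsed.

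**Analytic check.** The same noncentrality λ is tested on 1 or on 6 degrees of freedom, with 5% critical values 3.84 and 12.59.

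- λ = 3.84 gives 50% power on 1 df and 26% on 6 df.
- λ = 7.85 gives 80% on 1 df and 52% on 6 df.

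Worked example, with 51 per arm (N = 102), odds ratio 2 and an assumed control distribution of 3/10/27/30/18/8/4%. The mean category proportions of the two arms have a sum of cubes of 0.049. The information on the log odds ratio is

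V = n² N / [3(N + 1)²] × (1 − 0.049) = (51² × 102) / (3 × 103²) × 0.951 = 8.336 × 0.951 = 7.93.

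λ = (ln 2)² × 7.93 = 0.4805 × 7.93 = 3.81, which gives 50% power on 1 df and 26% on 6 df.

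**Simulation.** Tie-corrected Wilcoxon rank-sum against Pearson chi-square on the 2x7 table, 8,000 trials per setting. Ranges are over the four control distributions.

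| Per arm | Effect | Rank test | Chi-square | Share of power kept |
|---|---|---|---|---|
| 51 | odds ratio 2 | 48–51% | 22–26% | 0.45–0.50 |
| 51 | odds ratio 2.5 | 70–74% | 40–44% | 0.55–0.59 |
| 51 | odds ratio 3 | 85–87% | 58–60% | 0.67–0.69 |
| 51 | 0.556 SD | 74–76% | 43–46% | 0.58–0.60 |
| 64 | odds ratio 2 | 58–60% | 29–31% | 0.51–0.52 |
| 64 | odds ratio 2.5 | 80–83% | 52–55% | 0.63–0.66 |
| 64 | odds ratio 3 | 92–94% | 71–73% | 0.76–0.78 |
| 64 | 0.556 SD | 83–85% | 55–58% | 0.66–0.68 |

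Separate simulations give nearly the same values with 51 per arm: about 23% against 50% at odds ratio 2, and about 57% against 86% at odds ratio 3. At odds ratio 1.5 the relative loss is larger, but both tests are weak (8–11% against 20–21%).

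The Fisher test on the 2x7 table (Monte Carlo, 500 trials, 51 per arm) reaches 24–28% at odds ratio 2. Choosing Fisher over chi-square therefore does not recover the loss.

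**The case against.** **PGIC is not named in the rule.** Section 2.8 speaks only of categorical outcomes, and PGIC might be collapsed to improved or not improved before testing. That would remove the 6-degrees-of-freedom argument. The first half stands: coverage of PGIC follows from its description in section 2.6. The second half has no support, because no dichotomy of PGIC is mentioned, whereas the NPDS responder cut-offs are spelled out. The other route, ANCOVA as for the primary outcome, is closed by the separate sentence for categorical variables, and a rating of change has no baseline value of its own.

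**The loss depends on invented inputs.** This is true, and a range is given for that reason. The ratios move little across the four control distributions. They move more with effect size and with the number per arm. Because the full analysis set with multiple imputation is planned, the results for 64 per arm deserve as much attention as those for 51.

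**Direction and sparse cells.** Tabulated category percentages would show which arm did better, and Fisher's test deals with sparse cells. Both points stand. The remaining defects are the lost power and the lack of an effect estimate.

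**Responder outcomes.** A reader might infer that the unadjusted tests of the three NPDS responder outcomes are also wrong. They are not. A 2x2 test is valid in a 1:1 randomised trial, and the compared percentages give direction and size. For the 11.5-point criterion, simulation with difference 11.5, SD 20.67 and an assumed baseline–change correlation of 0 to 0.5 gave chi-square power of 61–64% with 51 per arm. Logistic regression with baseline and sex gave 59–68%, a change of about −3 to +5 points. With 64 per arm the change is 0 to +9 points. The gain over Fisher's test is larger (+5 to +15 points), but that reflects Fisher's conservatism as well as the adjustment.

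**Multiple imputation.** A reader might also infer that Fisher or chi-square cannot be reconciled with the planned multiple imputation. The document does not say how results will be combined. Responder status can be derived from imputed NPDS scores and risk differences pooled, so no error is shown.

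**Conclusion.** The point holds for PGIC. As written, an ordered 7-category outcome is to be compared between arms with a test that disregards the order. For odds ratios of 2 to 3 and 51 to 64 per arm, the loss is about one quarter to one half of the ordinal test's power. At a latent shift equal to the trial's own standardised effect of 0.556, it is about 40% with 51 per arm and about one third with 64. This rests on assumed PGIC distributions, a one-directional shift and uncollapsed categories.

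Two stronger readings go too far. A general halving of power fits only odds ratios near 2 to 2.5 with 51 per arm, and near 2 with 64. Nor can it be said that PGIC would probably be inconclusive whenever a real shift exists: chi-square power passes 50% at odds ratio 3 with 51 per arm, and at 2.5 and 3 with 64. At odds ratio 2 even the rank test reaches only 48–60%.

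Only secondary outcomes are concerned. The primary ANCOVA result and the sample size do not depend on this rule.

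**What to change.** In section 2.8, take PGIC out of the general categorical rule and name one between-arm method for it. One choice is a Wilcoxon rank-sum test stratified by sex (van Elteren), which respects the sex-stratified allocation of section 2.2. The other is a proportional-odds model with arm and sex, reporting the common odds ratio with its 95% CI. The model has the advantage of giving an effect size. Keep Fisher or chi-square for nominal and binary variables.

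The change needs no new data and no more patients. Its small downside is that the proportional-odds assumption has to be checked if the model is used.

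Logistic regression of the NPDS responder outcomes on arm, baseline NPDS and sex is an optional refinement with little power gain over chi-square. It does not correct an error.
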